##### 2.4.4.3 Penetration and Sustainability

Factors affecting sustained implementation will be assessed using a quantitative online survey of staff who completed INFANT implementation training 24-months post-training. Qualitative interviews will be conducted with a purposeful sample of organizational staff (continued/discontinued implementation) to explore key factors influencing sustained implementation. Qualitative interviews with key state level partners will also be conducted to explore the extent to which dissemination and promotion was embedded into existing systems, and barriers/facilitators to achieving integration into routine practice.

##### 2.4.4.4 Costs

Costs of scaling up will be examined to assess intervention affordability and sustainability. A mixed-methods approach will evaluate the costs associated with implementation, using qualitative data collected from quarterly semi-structured interviews with key informants involved in implementation and unit costs and quantities by resource category (e.g., time, equipment).

##### 2.4.4.5 Reach

Intervention enrolment, participant characteristics, attendance and completion rates will be monitored over the duration of the project using the MCH nurse record system. Use of the app and website will be measured via analytics using an Engagement Index Score, a novel methodology previously developed by members of the research team (41).

#### 2.4.5 Data Analysis

Descriptive statistics will be reported for quantitative survey items related to organizational readiness, acceptability, appropriateness, feasibility, adaptation and penetration. Qualitative interview data will be transcribed verbatim and coded deductively [informed by CFIR (37), PSAT (38) and FRAME (39)] and inductively to capture issues within and outside of these frameworks. This has been successfully used by the team in previous implementation research (25, 42). Findings will be compared with the choice of INFANT implementation strategies to determine future refinements. Cost data analysis will use a healthcare funder perspective and detailed pathway analysis will specify scale-up and implementation activities in order to measure costs of associated resource use (2023 reference year, costs measured in Australian dollars (AUD)). Total and incremental cost, cost per local government area, cost per participant child and cost per eligible child will be reported.

### 2.5 Effectiveness Trial

#### 2.5.1 Trial Design

An embedded non-randomised controlled trial will assess the effectiveness and cost-effectiveness of INFANT when delivered at scale. The trial will involve comparing primary and secondary effectiveness outcomes between a group of INFANT participants (intervention arm) and a non-randomised comparison group recruited within the same communities prior to the implementation of INFANT (usual care arm). This approach enables comparison of outcomes between parents and infants exposed and not exposed to the intervention living in the same geographical areas and therefore sharing socio-demographic characteristics and having access to the same health services. The risk of bias will be reduced by replicating strategies for recruitment, follow-up and assessment in both trial arms and adjusting for unbalanced baseline characteristics. This trial design was deemed appropriate for assessing the effect of INFANT when implemented at scale in real-world conditions, enabling natural dissemination and uptake to be captured. A cluster randomized design with communities allocated to intervention or usual care was deemed not feasible because the prospect of being randomised to the control arm is likely to reduce participation. Within communities, the prospect of parent groups being randomised to a control arm is unethical (given the known efficacy of the intervention) and contamination between groups would be unavoidable. A stepped-wedge cluster randomised study design (43) was also considered but ruled out as randomisation of LGAs to an implementation time period may interfere with natural uptake under real world conditions.

#### 2.5.2 Eligibility Criteria

Parents will be eligible if they are a first-time parent/primary caregiver of an infant aged 0-3 months, owning an internet enabled personal mobile phone and able to communicate in English. Infants born before 37 weeks gestation will be excluded.

#### 2.5.3 Study Procedures

Families will be recruited over a 6-month period for the comparison arm and over a two-year period for the intervention group (**Table 1**). The comparison (usual care) group will be recruited prior to the implementation of INFANT by health services who have expressed interest prior to undergoing INFANT training. If sample size is not achieved from these LGAs, recruitment will be extended to other LGAs ensuring a mix of metro, regional, rural LGAs and various levels of socioeconomic disadvantage. There will be a three-month gap between recruitment of the last comparison participant and the commencement of recruitment for INFANT implementation participants. This gap ensures comparison participant infants will be too old to enroll in INFANT sessions and thus reduce potential for contamination.

Eligible parents will be invited to participate *via* SMS (with up to 2 reminders) sent by participating organisations. The SMS will contain a link to an online screening and consent process with consenting parents invited to complete online surveys when infants are aged ≤ 3 months (T1), 12 months (T2) and 18 months (T3) (**Table 1**). Up to three reminders will be generated for non-responders to follow up survey invitations. Strategies will be employed to promote retention (e.g. personalised newsletters, reimbursement for time spent completing surveys) which have been used successfully in the original INFANT trial, which achieved 85% retention over two years across both study arms (13).

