#### 2.5.6 Data Collection and Analysis

Infant diets will be measured by a validated Food Frequency questionnaire (FFQ) with average percentage categorical agreement against three days of 24 hour recall of 62-64% (49). Infant physical activity will be measured using a single parent-reported question with good test-retest reliability (ICC 0.62) (50). Infant screen time will be measured using a single parent-reported question with excellent reliability (ICC 0.84) (51). Change in BMIz measured at 12 and 18 months will be derived from child height and weight which is routinely collected by MCH nurses and will be made available in de-identified form to the research team. These data are typically available for 80% and 71% of infants at 12 and 18 months respectively (52). Lifestyle pattern scores will be calculated as linear combinations of the standardized dietary (fruit, vegetables, water, discretionary sweet foods, discretionary savory foods), outdoor and television viewing items, using the principal component analysis factor loadings previously published from the combined INFANT and INFANT Extend datasets (44).

Covariates will include self-reported parent socio-demographic characteristics (including marital status, education level, age, sex, Indigenous status, language spoken at home, country of birth, years lived in Australia, health care card holder) parent weight and height, pre-pregnancy weight, self-rated coping, sleep and health, infant sex, birth weight and temperament. Baseline characteristics will be compared between arms using linear mixed models (LMM) or generalized estimating equations (GEE) with link and distribution selected based on the type of variable. The effect of the intervention on the primary outcome (‘Discretionary food and screen time’ lifestyle pattern) will be estimated using a LMM including arm, time (12 and 18 months), interaction arm-time and any baseline variable showing clear imbalance between arms (covariates) as fixed effects. The same LMM model will be used for numerical secondary outcomes. All mixed models will include MCH group as a random effect to account for clustering. The effect of the intervention on proportion of mothers with any breastfeeding at 12 months will be estimated using a GEE model with logit link and binary distribution including arm, time (12 and 18 months), interaction arm-time and baseline confounders. If appropriate, multiple imputation will be used to handle missing data.

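### The arms differ in season and calendar period by design, and the stated model commits to adjusting for neither

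*Protocol article*

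**What the plan says.** Section 2.5.3 (Study Procedures) sets the recruitment windows: "Families will be recruited over a 6-month period for the comparison arm and over a two-year period for the intervention group". It places a "three-month gap between recruitment of the last comparison participant and the commencement of recruitment for INFANT implementation participants". Section 2.5.1 (Trial Design) confirms that the comparison families come from before implementation. Surveys are tied to infant age: up to 3 months, 12 months and 18 months.

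Section 2.5.6 (Data Collection and Analysis) gives the primary model as an "LMM including arm, time (12 and 18 months), interaction arm-time and any baseline variable showing clear imbalance between arms (covariates) as fixed effects". Time here means infant age, not date. It adds: "All mixed models will include MCH group as a random effect to account for clustering". The covariate list opens with "Covariates will include self-reported parent socio-demographic characteristics" and goes on to parental anthropometry and self-rated health, and to infant sex, birth weight and temperament. It contains no month, season or date.

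The stated protections against bias are recruitment in the same communities, "replicating strategies for recruitment, follow-up and assessment in both trial arms", and adjustment for unbalanced baseline characteristics. The Discussion repeats these and concedes that a non-randomised design has limitations, but it names neither season nor period.

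**The concern.** Because outcomes are measured at fixed ages, the recruitment calendar carries straight through to the assessment calendar. A seasonal cycle averages out over the intervention arm's 24 months but not over the comparison arm's 6. A trend over the years separates the arms by the distance between their recruitment midpoints. The planned model would attribute either difference to arm.

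The lifestyle pattern scores are built from fruit, vegetable, water, discretionary food, outdoor and television items. Screen use and physical activity are also analysed separately. It is plausible that some of these vary over the year.

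The listed protections do not reach the problem. Identical procedures in the same communities still take place at different times. The parent groups are recruited in separate periods and so are nested within arm, which means the group random effect cannot absorb a period difference. At stake is whether a difference of the size the trial is powered for, 0.17 points, can be attributed to INFANT.

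**Working it through.** **Inputs from section 2.5.5 (Sample Size).** 1,000 complete infants per arm, mean group size 5.4, coefficient of variation 0.32, ICC 0.048, SD 1.21, target difference 0.17, two-sided alpha 0.05.

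**Reproducing the plan's figure.** Design effect = 1 + ((0.32² + 1) × 5.4 − 1) × 0.048 = 1.238. SE = 1.21 × √(2 × 1.238 / 1,000) = 0.060. Power at 0.17 = 80.6% with 1.21 taken as the total SD. With 1.21 taken as the within-cluster SD, power is 78.7%. The stated 80% is reproduced, and SE 0.060 is used below.

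**Calendar separation.** With even accrual (assumed), comparison recruitment spans months 0 to 6 and intervention recruitment months 9 to 33. The midpoints are months 3 and 21, which are 18 months apart with no overlap.

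**Seasonal bias at 18 months.** Take an annual cosine of amplitude A (assumed). Its mean over a 24-month window is zero. Over a 6-month window it is at most (2/π)A = 0.637A. If age at enrolment is also spread evenly over 0-3 months, multiply by 0.900, giving 0.573A. These are maxima over the unknown phase. The bias is zero if the window is centred on the midpoint of the cycle.

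| A (assumed) | Worst-phase bias | Type I error, worst phase | Type I error, averaged over phase |
|---|---|---|---|
| 0.05 | 0.029-0.032 | 8% | 6-7% |
| 0.10 | 0.057-0.064 | 16-18% | 10-12% |
| 0.20 | 0.115-0.127 | 48-56% | 27-31% |

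The 12- and 18-month assessments are half a year apart, so a single annual cycle biases them in opposite directions. A seasonal artefact could therefore also appear in the arm-by-time interaction.

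**Cost of season terms.** Variance inflation (VIF) from one sine and cosine pair is 1 + (f/2)² / v. Here f is the seasonal factor and v is the within-arm variance of the harmonic, averaged over arms.
- f = 0.573: v = mean(0.172, 0.5) = 0.336, so VIF = 1 + 0.082/0.336 = 1.24, SE +11-12%, power at 0.17 about 72%.
- f = 0.637: v = mean(0.095, 0.5) = 0.297, so VIF = 1 + 0.101/0.297 = 1.34, SE +16%, power about 68%.

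**Cost of a linear date term.** Within-arm variances of date are 6²/12 = 3 and 24²/12 = 48, mean 25.5. VIF = 1 + 9²/25.5 = 4.18. With season terms as well, regressing arm on all the terms over an evenly spaced design gives VIF 5.0-5.3 and power at 0.17 of about 23-24%.

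**Secular drift.** An assumed 0.04 points per year over 1.5 years is 0.06 points. With no intervention effect, that gives a type I error of about 17%.

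**The case against.** The strongest reply is that every bias figure rests on an assumed amplitude or trend. That is correct. The protocol supplies neither, and the worst-phase figures need the comparison window to be centred on a seasonal peak or trough. A reader might infer that the trial's false-positive rate is near 50%, or that its result will be biased in a known direction. The documents support neither reading.

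Seasonality is also less obvious for the primary score than for the secondary pattern named for fruit, vegetables and outdoor time. The item loadings are not given, and no seasonal reason is apparent for breastfeeding or BMIz. This stands, and it limits which outcomes need the adjustment.

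The clause admitting any clearly imbalanced baseline variable could let season of recruitment in. That is possible, but the clause does not commit to it and the covariate list points elsewhere. Nor is this a detail left to the analysis plan, because the article itself fixes the model and the covariates.

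Section 2.5.1 explains the before-implementation comparison and why randomised alternatives were rejected. The design choice is disclosed and is not disputed here. The point concerns what the analysis does about its consequences.

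Finally, a reader might infer that a date term would settle the secular question. It would not. Its slope would come mainly from the intervention cohort, where the protocol expects local adaptation and natural uptake. Changing delivery would then be read as background trend, and about three analyses in four would miss a true 0.17-point effect.

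**Conclusion.** The concern holds as a gap in the stated analysis, not as a demonstrated bias. The recruitment windows guarantee that season and calendar period differ by arm, and nothing in the model is committed to handling either. The potential size is material: an assumed amplitude of 0.10 points could move the 18-month contrast by up to about 0.06, roughly a third of the 0.17 target. The actual size and direction cannot be determined from the protocol.

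The two parts differ in how far they can be repaired. Season can be estimated because the intervention arm covers every month, provided accrual is reasonably even. Secular change is nearly aliased with arm and can only be bounded. The conclusions assume even accrual, a single annual cycle, and the protocol's own variance inputs.

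**What to change.** 1. **Season.** Pre-specify a season-adjusted analysis, with annual sine and cosine of assessment date estimated across both arms, for the primary score and the diet, screen and activity outcomes. Report it beside the planned model, and state that the conclusion depends on season if the two disagree. This needs assessment dates. The article does not say these are recorded, but age-timed online surveys imply it.
2. **Period.** Do not rely on a linear date term. Pre-specify a sensitivity analysis that shifts the arm effect over a stated range of drift across the 18 months between recruitment midpoints, for example 0.04 points per year = 0.06 points. Report the drift that would overturn the conclusion. As an illustration, an observed effect of 0.17 with SE 0.060 loses significance once drift in its favour exceeds 0.17 − 1.96 × 0.060 = 0.052 points, or about 0.035 per year.
3. **Discussion.** Name season and period effects as limitations of the non-concurrent comparison.

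No new recruitment is needed. The cost is precision in the season-adjusted model: SE up by 11% to 16%, and power at 0.17 of about 68-72%. For that reason it is reported beside the planned model and does not replace it. The drift analysis needs no extra data, but it bounds the problem without removing it.

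### The same-community premise is not secured by comparison-arm recruitment, and the primary model names no LGA or area term that would restore it

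*Protocol article*

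**What the plan says.** Section 2.5.1 of the protocol article justifies comparing families recruited before and after implementation on the ground that they are "living in the same geographical areas and therefore sharing socio-demographic characteristics and having access to the same health services". The Discussion (section 3) lists same-community recruitment first among the ways of limiting the weaknesses of a non-randomised design.

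Section 2.5.3 takes comparison families first from services that have expressed interest but have not yet been trained. It then provides a fallback: "If sample size is not achieved from these LGAs, recruitment will be extended to other LGAs", with a spread of metropolitan, regional and rural areas and of disadvantage to be ensured. The recruitment periods differ: "Families will be recruited over a 6-month period for the comparison arm and over a two-year period for the intervention group". Section 2.4.4.1 plans interviews with organisations that express interest or train staff but do not go on to implement.

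Section 2.5.6 gives the primary analysis as an "LMM including arm, time (12 and 18 months), interaction arm-time and any baseline variable showing clear imbalance between arms (covariates) as fixed effects". On clustering it says: "All mixed models will include MCH group as a random effect to account for clustering". The socio-demographic covariates it names are "marital status, education level, age, sex, Indigenous status, language spoken at home, country of birth, years lived in Australia, health care card holder". Parental weight and height, coping, sleep, health and infant characteristics follow. No item is an LGA, a region, a remoteness class or an area-disadvantage index.

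**The concern.** Without randomisation, shared geography is one of the main safeguards the design offers. Recruitment does not guarantee it, for three reasons.

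- The fallback LGAs need not supply any intervention families.
- Some interested services may contribute comparison families and then never implement.
- Even LGAs present in both arms may carry different weights over six months and over two years.

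The model would have to make up for this and, as stated, it does not. Area differences in diet or screen time could then be read as an effect of INFANT, or could hide one. The Introduction itself says that these behaviours are patterned geographically and socioeconomically.

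**Working it through.** **1. Does the MCH-group random effect give a within-area comparison?** The sample-size section takes first-time parent groups as the clusters, 190 in each arm. The arms are recruited in sequence with a three-month gap, so each group belongs to one arm and sits within one area. A random intercept for such a group adjusts the standard error for clustering. It does not compare intervention and comparison families within an LGA.

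**2. The stated power.** Inputs from section 2.5.5: 1,000 infants per arm, 190 groups of 5.4 (1,026), difference 0.17, SD 1.21, ICC 0.048, CV of group size 0.32, two-sided alpha 0.05.

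- Design effect = 1 + ((1 + 0.32²) × 5.4 − 1) × 0.048 = 1.238.
- SD 1.21 read as the within-cluster SD: total SD = 1.21/√(1 − 0.048) = 1.240. SE = √(2 × 1.240² × 1.238/1,000) = 0.0617. Power = Φ(0.17/0.0617 − 1.96) = 78.7%, or 79.7% with 1,026 per arm.
- SD 1.21 read as the total SD: 80.6%, or 81.6% with 1,026 per arm.

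The stated 80% therefore reproduces. Its ICC is for parent groups only.

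**3. Shift in the estimate if the LGA mix differs.** Let f be the share of the comparison arm from LGAs with no intervention families, and D the difference in mean score between those LGAs and the shared ones, after covariates. The shift is f × D. The documents give neither quantity, so both are assumed. Percentages are of 0.17.

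| | D = 0.1 | D = 0.2 | D = 0.3 |
|---|---|---|---|
| f = 10% | 0.010 (6%) | 0.020 (12%) | 0.030 (18%) |
| f = 25% | 0.025 (15%) | 0.050 (29%) | 0.075 (44%) |
| f = 50% | 0.050 (29%) | 0.100 (59%) | 0.150 (88%) |

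With f = 0 and equal LGA weights in both arms, the shift is zero.

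**4. Precision.** Because the arms are sequential, variation of LGA means between periods is LGA-by-arm variation. With L LGAs contributing to both arms and an LGA-by-period ICC ρ (both assumed), the variance of the arm difference becomes 0.0609² + 2 × ρ × 1.24²/L, where 0.0609 is the SE behind the 79.7% above.

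- L = 30: power at 0.17 is 74% (ρ = 0.005) or 70% (ρ = 0.01).
- L = 15: 70% or 61%.

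Separately, suppose stable LGA differences make up 0.005-0.02 of total variance, with 10-40 LGAs and f of 25-50%. If the model's SE stayed at 0.0617, the true type I error would be about 0.052-0.12. With f = 0 and equal weights it stays at 0.05.

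**The case against.** The case on the other side has five parts.

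- **The fallback carries a safeguard.** It asks for a spread of remoteness and disadvantage, and INFANT is promoted to all 79 LGAs, so a fallback LGA may later supply intervention families. This stands as mitigation. It is not matching, and nothing requires the overlap.
- **Area could still enter the model.** A reader might infer that an area variable is shut out altogether. The document does not support that: the rule covers any baseline variable with clear imbalance, the socio-demographic list is introduced as illustrative, and an analysis plan not shown here could name LGA. What stands is narrower. The model as stated names no area term, and its adjustment depends on observed imbalance.
- **Individual covariates may absorb area differences.** Education, language, country of birth and health care card status probably do so in part, if they meet the imbalance rule.
- **The large figures are assumed.** A 0.3-point area gap is as large as the 0.29 effect quoted from the earlier trial. It also exceeds the between-group SD implied by the plan, √0.048 × 1.24 = 0.27. It belongs at the upper end of a range. Nor do the documents show that true power is 61-74%, since they give no LGA-level ICC and no count of recruiting LGAs.
- **The standard error can err either way.** Where LGAs contribute to both arms, stable LGA effects cancel in the contrast. Leaving LGA out then places that variance in the group component and can make the standard error too large.

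**Conclusion.** The point holds as a mismatch between the design rationale and the stated primary analysis. Both arms are meant to come from the same communities, recruitment allows otherwise, and the model does not make the within-community comparison. Bias is conditional. It needs an LGA mix that differs between arms, through the fallback, through interested services that never implement or through unequal weights. It also needs an area difference left over after covariate adjustment. Its direction and size cannot be derived from the documents; 0.01-0.15 points (6-88% of 0.17) is an assumed range, not an estimate. The sample size is not wrong on its own inputs. It makes no allowance for LGA-by-period variation.

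**What to change.** In section 2.5.6:

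- Add LGA to the primary model, as a fixed effect or a random intercept, with MCH group nested within LGA. A fixed effect removes stable LGA differences fully; a random intercept still uses some between-LGA information.
- If LGA-by-period variation is to be reflected in the standard error, add a random LGA-by-arm term. An LGA fixed effect alone does not do this.
- Prespecify remoteness and area disadvantage as covariates irrespective of observed imbalance. They matter most with a random LGA intercept, because LGA fixed effects already absorb whatever is constant within an LGA.
- Add a prespecified sensitivity analysis restricted to LGAs that contribute to both arms.

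Leave the recruitment fallback as it is. Limiting it to interested LGAs would largely remove it and put the target of 1,500 per arm at risk.

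The cost is some precision, because one-arm LGAs contribute little to a within-LGA estimate. The loss grows if the fallback is used heavily. LGA or postcode must also be recorded for each family: Table 2 lists postcode only among aggregated reach data, so individual-level capture should be confirmed.

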### 2.2 INFANT Enhancements for Scale Up

**Figure 1** provides an overview of the evolution of INFANT from efficacy testing to state wide scale up. Small scale translation of INFANT across eight Victorian LGAs between 2011-2016 (25) identified a number of barriers to real-world implementation and scale up. These included a high organisational administrative burden coordinating and scheduling group sessions; challenges faced by facilitators in attending face-to-face training; limited staff time and confidence for evaluation (15); parents’ earlier return to work (between 9-12 months as opposed to 15-18 months in the original trial); and parental preference for online supplementary information (15, 26). These findings have informed a number of enhancements to INFANT to improve scalability. These include the provision of online facilitator training, accessible to MCH nurses, dietitians and other health professionals; a reduction in INFANT group sessions from six to four (3, 6, 9, 12 months) to accommodate parents’ earlier return to work; and the development of the My Baby Now app (27, 28). The app provides evidence-based information and support from birth to 18 months of age including two to three age-appropriate push notifications per week to reinforce INFANT key messages (**Box 1**; **Supplementary File 1**). The information from the trial (originally provided *via* handouts and a DVD) has been incorporated into the app, including information from sessions five and six offered at 15 and 18 months in the original trial. Additional information on milk feeding, including a new key message ‘feeding is a learning curve’, was also added to the app and program resources. An overview of the INFANT group sessions and key features of the My Baby Now app are provided in **Supplementary Files 2****,**
**3**.

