**Figure 1 f1:**
[figure not shown]
Evolution of INFANT program from efficacy testing to state wide scale up.

To reflect the move from trial phase to scale up, the acronym INFANT was changed from ‘Infant feeding activity and nutrition trial’ to INfant Feeding, Active play and NuTrition. Health services will be encouraged to offer the app from birth aligned with routine services and through INFANT group sessions starting at 3 months of age. Promotion of the app will be *via* flyers and posters in health services, and SMS and referral during MCH key age and stage consultations. Enrolment of parents to the group sessions will be *via* existing systems for group programs locally. In the original RCT, this involved inviting first time parent groups to continue to meet for INFANT sessions. In the small-scale translation study, areas continued to use this approach, with some making the last session of the first-time parent group (usually when infants were around three months old) the first INFANT session. This opt-in model of enrolment was identified as promoting intervention uptake with parents (26).

Box 1INFANT key messages.

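### The three-month gap cannot guarantee that comparison infants are too old for INFANT sessions (they are 3 to 12 months old at the earliest launch), and it does not limit their exposure to the app

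*Protocol article*

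**What the plan says.** Eligible parents are the "first-time parent/primary caregiver of an infant aged 0-3 months" (section 2.5.2). On timing, section 2.5.3 states: "Families will be recruited over a 6-month period for the comparison arm". It continues: "There will be a three-month gap between recruitment of the last comparison participant and the commencement of recruitment for INFANT implementation participants". The purpose follows directly: "This gap ensures comparison participant infants will be too old to enroll in INFANT sessions and thus reduce potential for contamination".

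Section 2.2 describes what is delivered and when. Scale-up involves "a reduction in INFANT group sessions from six to four (3, 6, 9, 12 months"), plus an app covering birth to 18 months. Services are encouraged to "offer the app from birth aligned with routine services and through INFANT group sessions starting at 3 months of age". The app is promoted with flyers and posters in health services and by "SMS and referral during MCH key age and stage consultations". Session places are filled through local systems for group programs. In the earlier studies this meant inviting first-time parent groups to carry on meeting, and some areas used the last meeting of such a group, at around three months, as the first INFANT session.

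Section 2.5.1 places both arms in the same communities. Section 2.5.4 sets the primary outcome at 18 months of age.

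**The concern.** The gap is the only safeguard against contamination that section 2.5.3 describes, and the article treats contamination as important: section 2.5.1 rejects randomising parent groups within communities partly because contamination would be unavoidable. The sentence in section 2.5.3 promises an age separation that the dates and ages do not give. It also addresses only one of the two components that the Abstract names.

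Comparison families go on using the same services. The Introduction reports that over 80% of Victorian parents still attend MCH consultations at 12 months, and these consultations are a channel for promoting the app. Section 2.4.4.1 also surveys trained staff on using the core INFANT messages in their practice, so some spread through nurses is foreseeable.

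If comparison families take up part of INFANT and benefit from it, the primary difference shrinks. A null result would then be hard to read: it could reflect an ineffective program or a diluted comparison. The trial-based and modelled economic evaluations in section 2.5.7 rest on the same contrast between arms.

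**Working it through.** **Age at launch.** Launch here means the opening of intervention recruitment, the earliest point the article fixes.

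Age at launch = age at recruitment (0 to 3 months, section 2.5.2) + time from recruitment to the end of the window (0 to 6 months, section 2.5.3) + gap (3 months, section 2.5.3).

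- Last recruits, newborn: 0 + 0 + 3 = 3 months. Session ages still to come: 3, 6, 9, 12.
- Last recruits, aged 3 months: 3 + 0 + 3 = 6 months. To come: 6, 9, 12.
- First recruits, newborn: 0 + 6 + 3 = 9 months. To come: 9, 12.
- First recruits, aged 3 months: 3 + 6 + 3 = 12 months. To come: 12.

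The range is 3 to 12 months. The youngest infants are exactly at the age of the first session and none is past the age of the last.

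**How many are near the entry age.** Assume that recruitment date and age at recruitment are uniform and independent (the article does not say). The excess over 3 months is then U(0,6) + U(0,3).

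- Aged 3 to 4 months at launch: (1 × 1 / 2) / 18 = 2.8%.
- Aged 3 to 6 months at launch: (3 × 3 / 2) / 18 = 25%.

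**App.** The app range ends at 18 months and the oldest comparison infant is 12 months at launch, so all are within it. Time left to the primary outcome is 18 − 12 = 6 months for the oldest and 18 − 3 = 15 months for the youngest.

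**Would a longer gap solve it?** With a gap of g months the range is g to g + 9. All infants are past the last session age only if g exceeds 12, and past the app range only if g exceeds 18. An 18-month gap would need at least 6 + 18 + 24 + 15 = 63 months from first comparison recruitment to the last 18-month survey, against the five years (60 months) in section 2.3.

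**The plan's power figure.** Inputs from section 2.5.5: 1,000 per arm, 5.4 children per group, coefficient of variation 0.32, ICC 0.048, SD 1.21, difference 0.17.

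- Design effect = 1 + ((1 + 0.32²) × 5.4 − 1) × 0.048 = 1.238.
- Effective n per arm = 1,000 / 1.238 = 808.
- Power = 80.6% with 1.21 as the total SD, or 78.7% with it as the within-cluster SD. The stated 80% is reproduced.

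**Illustration of dilution.** Let a share c of the comparison arm receive the full effect δ. The expected difference becomes δ(1 − c). Calibrating to exactly 80% power gives SE = 0.17 / (1.960 + 0.842) = 0.0607, and power = Φ(δ(1 − c) / 0.0607 − 1.96).

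- δ = 0.17, c = 10%: difference 0.153, power 71%.
- δ = 0.17, c = 20%: difference 0.136, power 61%.
- δ = 0.17, c = 30%: difference 0.119, power 50%.
- δ = 0.29 (earlier trial, section 2.5.5), c = 30%: difference 0.203, power 92%.

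Starting from the design-effect calculation (80.6%), the first three become 72, 62 and 51%. The shares are not in the article; they show sensitivity and are not a forecast.

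**The case against.** The best defence is that section 2.5.3 speaks of enrolling, not of attending. Section 2.2 suggests that families enter at about 3 months through first-time parent groups, with later sessions continuing a group already formed. Every comparison infant is at least 3 months old at launch, and under the uniform assumption only 2.8% are between 3 and 4 months. On that reading the gap does most of what is claimed for sessions. This part stands. But the article states no upper entry age (0 to 3 months is the rule for joining the study), and the youngest infants are at the entry age even so. The defence does not reach the app.

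Four stronger readings are tempting, and the document does not support them:

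- *The plan claims contamination is absent.* It says only that the potential is reduced, and only for sessions. For the app this is a gap in the reasoning, not a contradiction.
- *Every comparison child will be followed in an area running INFANT.* Section 2.5.3 lets comparison recruitment extend to other LGAs, which need not adopt; intervention recruitment runs for two years; and the Discussion treats organisational uptake as uncertain. The 6 to 15 months is the most exposure possible, in areas that adopt early.
- *The trial has no check on exposure.* A journal article need not list survey items or sensitivity analyses. Section 2.4.4.5 already tracks attendance through MCH records and app use through analytics, though it does not mention using these for comparison participants.
- *Power will fall by the amounts shown.* Being within the app's age range is not the same as using it, and an infant whose family finds the app late and attends no session is unlikely to receive the full effect.

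Dilution of this kind also would not create a false positive.

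**Conclusion.** The concern holds in limited form. The 3-to-12-month range follows exactly from the article's figures, so the word *ensures* is not supported for sessions, and the gap places no limit on app exposure. How many comparison infants could join a session depends on an entry rule that the article leaves open: a small edge group if entry is only at about 3 months, more if later joining is allowed.

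The likely consequence is bias of the primary contrast towards null, assuming that INFANT exposure helps comparison children in the same direction as intervention children. Its size cannot be derived from the document. It could matter if the true effect is near the detectable 0.17, and much less if it is near the 0.29 seen earlier, which came from a six-session version.

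**What to change.** 1. In section 2.5.3, replace the guarantee with the actual age range at the earliest launch (3 to 12 months). Reconcile it with the session ages and app range in section 2.2, state at what ages families can join sessions, and say plainly that the gap does not address the app.
2. Add items to the existing T2 and T3 surveys in both arms: INFANT sessions attended, and use of My Baby Now with the infant's age when use began.
3. Pre-specify a sensitivity analysis that reports comparison-arm exposure and repeats the primary contrast taking it into account, for example by timing of LGA adoption or by excluding exposed comparison participants. Interpret it cautiously, because families and services choose their exposure.

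Two other remedies may come to mind, and I would not use them. Treating arm as an instrument for exposure is unsound here, because arm is neither randomised nor concurrent, so differences in period and selection would be rescaled rather than removed. Restricting first session intake by birth date would interfere with the natural uptake that section 2.5.1 sets out to capture.

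The cost is a wording change, a few survey questions and one extra analysis. Exposure not recorded at T2 and T3 would later have to be recovered by recall or from incomplete app records.
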